#### Timeline

We intend to begin data collection as soon as the current registered report is granted in-principle acceptance and project that all data will be collected and analyzed within a calendar year from that date. If the results of the Stage 1 review warrant major revision of the proposed experimental procedures, we intend to resubmit the report for Stage 1 review within one month after receiving reviewers’ feedback.

#### COVID-19 contingency plan

The global COVID-19 pandemic is currently preventing us from testing participants in the lab. We are transitioning the experiments in this report to Lookit–an online platform for developmental research. Using this platform, we will be able to record participants’ eye movements using web-cameras in their desktop or laptop computers and subsequently code their looking behavior manually. While the reportedly higher data loss rate may slow our data collection, Lookit’s access to a larger sample of participants and at-home participation is likely to offset its associated data loss.

#### Apparatus

A Tobii T60XL corneal-reflection eyetracker will be used for stimulus presentation and data collection. The eyetracker has a sampling rate of 60 Hz, and a display size of 57.3 × 45 cm.

#### Stimuli

Infants will view a series of four video-taped vignettes, each featuring a new novel word-object pairing. Each video begins with an actor pointing three familiar objects, naming each with its familiar basic-level noun. Next the actor looks toward an object hidden behind her back, naming it with a novel word. See Fig 1 for a representation of a single trial and S3 Appendix for a complete list of stimuli. All stimuli will be made available on Open Science Framework.

**Fig 1 pone.0244968.g001:**
[figure not shown]
A representative example of visual and linguistic information presented in each phase in the semantic priming condition.

#### Stimulus selection and design

We used vocabulary norms [36] to select the visual and linguistic materials. For the familiar objects presented in the Priming phase, we selected objects whose names are understood by at least 60% of 15-month-olds (nouns: apple, banana, orange, jacket, sock, hat, truck, car, bus, cat, dog, horse). For the novel objects presented during Test, we (a) selected objects whose names infants do not understand (e.g., rare tropical fruits, exotic animals), and (b) chose pairs of objects from distinct semantic neighborhoods (e.g., papaya vs aardvark).

#### Procedure

All infants will participate in 4 trials, each including a Priming and a Test phase (Fig 1). Each trial will include one novel object-novel word pairing. Infants will be assigned randomly to condition. What varies across conditions is the first three objects presented during Priming: in the Semantic Priming and Follow-up Control conditions, these are all members of the same semantic neighborhood (e.g., animals, food, clothing); in the No Priming condition, they are from different semantic neighborhoods. We selected a between-subject design to avoid potential carry-over effects, which would dilute the predicted advantage of Semantic Priming. Another solution to minimize carry-over effects might be to increase the number of trials and to present them as blocks. However, doing so would lengthen the procedure and therefore runs the risk of exceeding infants’ attention. In all conditions we provided infants with rich communicative and referential cues to support their interpretation of Trial 4 of the Priming phase, in which the object is hidden, as a labeling episode as well.

Semantic Priming condition (*N* = 24; Fig 1): Priming (35 s): During Priming an actor will point to and name three familiar objects, all from the same semantic neighborhood (fruits, clothing, vehicles, animals). The objects will appear one at a time, behind the actor; the actor will turn to point to and name them, using their familiar basic-level nouns (e.g., “Look! An apple! Do you see the apple?”). A fourth object, seemingly unintentionally occluded by the actor’s body, will be labeled with a novel noun (e.g. “Look, a *modi*!”), creating a situation of abstract reference—during naming, no referent object is visible. The actor will alternate between looking to the object and to the camera to indicate that the referent object is located behind her. We present infants with familiar word-object pairs during the priming phase to access their resident semantic knowledge [30,37–39].

Test (10 s): During Test, infants first will see an attention getter (2 s), followed by a blank white screen (2 s), during which they will hear the first prompt to look to the object corresponding to the novel label, e.g., “Now look! Where is the modi?”. Immediately after, two objects will appear side-by-side—one is a member of the same semantic neighborhood during the Priming phase (e.g., a novel fruit) and the other is a semantically distant item (e.g., a novel furniture item). With these objects visible, infants will hear, e.g., “Can you find the modi?”.

No Priming condition (*N* = 24; Fig 2): The procedure will be identical to the Semantic Priming condition, except that during Priming, infants will be presented with familiar word-object pairs, all from different semantic neighborhoods (e.g., a hat, truck, and horse). Thus, no priming of any particular semantic neighborhood will be involved.

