## Abstract

Human language permits us to call to mind objects, events, and ideas that we cannot witness directly. This capacity rests upon abstract verbal reference: the appreciation that words are linked to mental representations that can be established, retrieved and modified, even when the entities to which a word refers is perceptually unavailable. Although establishing verbal reference is a pivotal achievement, questions concerning its developmental origins remain. To address this gap, we investigate infants’ ability to establish a representation of an object, hidden from view, from language input alone. In two experiments, 15-month-olds (*N* = 72) and 12-month-olds (*N* = 72) watch as an actor names three familiar, visible objects; she then provides a novel name for a fourth, hidden fully from infants’ view. In the Semantic Priming condition, the visible familiar objects all belong to the same semantic neighborhood (e.g., apple, banana, orange). In the No Priming condition, the objects are drawn from different semantic neighborhoods (e.g., apple, shoe, car). At test infants view two objects. If infants can use the naming information alone to identify the likely referent, then infants in the Semantic Priming, but not in the No Priming condition, will successfully infer the referent of the fourth (hidden) object. Brief summary of results here. Implications for the development of abstract verbal reference will be discussed.

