#### Proportion of LT to the target

Semantic Priming condition: We predict significant effects of Condition, with average proportion of LT (across 6 s) to the target significantly higher in the Semantic Priming than in the No Priming and Follow-up Control conditions. Further, we predict that if infants successfully infer the meaning of the novel word and establish a representation of its referent in the Semantic Priming condition, their LT to the target will be significantly above chance (50%).

No Priming condition: If infants’ looking behavior is influenced by semantic inferences, rather than baseline preferences, then their LT to both objects in the No Priming condition will be equivalent and will not deviate significantly from chance. We predict this because there is no basis for infants to infer the meaning of the novel word after being presented with three semantically distant word-object pairs.

Follow-up Control condition: If infants’ looking preference in the Semantic Priming condition is the result of the semantic relations among the objects themselves, then their performance in the Follow-up Control condition will not differ from the Semantic Priming condition. Conversely, if infants’ looking in the Semantic Priming condition reflects infants’ inferences about novel word meanings, their LT in the Follow-up Control condition should not significantly deviate from chance.

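### Taking the No Priming objects from three different neighborhoods does not guarantee a baseline that is neutral between the two test objects

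*Protocol article*

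**What the plan says.** The familiar nouns are listed under Stimulus selection and design: "apple, banana, orange, jacket, sock, hat, truck, car, bus, cat, dog, horse". That is twelve nouns, three in each of four neighborhoods. The Semantic Priming paragraph of the Procedure confirms the four, with the primes of a trial "all from the same semantic neighborhood (fruits, clothing, vehicles, animals".

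In the No Priming condition the three primes are "all from different semantic neighborhoods (e.g., a hat, truck, and horse"). The Abstract gives another illustration: "the objects are drawn from different semantic neighborhoods (e.g., apple, shoe, car"). From the fact that the primes differ from one another, the Procedure concludes: "Thus, no priming of any particular semantic neighborhood will be involved".

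Test pairs are illustrated in two ways. Under Stimulus selection and design the authors "chose pairs of objects from distinct semantic neighborhoods (e.g., papaya vs aardvark"). In the Test paragraph of the Procedure one object is a novel fruit and "the other is a semantically distant item (e.g., a novel furniture item").

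The predictions for the proportion of looking time rest on this neutrality. Looking to the two objects in No Priming "will be equivalent and will not deviate significantly from chance", and Semantic Priming is predicted to exceed No Priming. The Follow-up Control paragraph also reads that condition against No Priming. Experiment 2 takes over the stimuli and the analyses.

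**The concern.** The stated criterion governs how the primes relate to each other. What makes a baseline neutral is how they relate to the target and the distractor. A trial can use three mutually unrelated primes and still name the neighborhood of exactly one test object. The infant then has a cue, weaker than in Semantic Priming, that favors one side.

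Three readings of the data depend on this baseline:

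- **Semantic Priming minus No Priming.** A distractor-side prime would lower No Priming and inflate the contrast; a target-side prime would raise No Priming and shrink it.
- **No Priming against 50%.** A one-sided cue undermines the stated reason for expecting chance-level looking.
- **Follow-up Control against No Priming.** A shifted comparator changes what a difference, or its absence, means.

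The comparisons of Semantic Priming with 50% and with Follow-up Control do not use this baseline.

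**Working it through.** The plan gives no figure to reproduce here. The check is an enumeration, followed by the plan's own examples and an illustration of scale.

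**Inputs.** Four prime neighborhoods (fruit, clothing, vehicle, animal), from Stimulus selection and design and the Procedure. Three primes per No Priming trial, each from a different neighborhood, so 4 − 3 = 1 is left out. The distractor is either one of the four (animal) or outside them (furniture).

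**Step 1: both test objects within the four.** There are four choices of neighborhood to leave out.

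| Left out | Target's neighborhood named | Distractor's neighborhood named |
|---|---|---|
| Target's | no | yes |
| Distractor's | yes | no |
| Either of the other two (2 choices) | yes | yes |

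Target only: 1/4. Distractor only: 1/4. Both: 2/4. Neither: 0. Over 4 × 3 = 12 ordered target–distractor pairs and 4 omissions, the 48 cases split 12, 12, 24 and 0.

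**Step 2: distractor outside the four.** The target's neighborhood is named unless it is the one left out: target only in 3/4, neither in 1/4. Over 4 targets and 4 omissions, the 16 cases split 12 and 4.

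**Step 3: the plan's examples, with the fruit as target.**

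| Primes | Test pair | Test object whose neighborhood is named |
|---|---|---|
| hat, truck, horse | papaya vs aardvark | distractor only (horse) |
| apple, shoe, car | papaya vs aardvark | target only (apple) |
| apple, shoe, car | fruit vs furniture | target only (apple) |
| hat, truck, horse | fruit vs furniture | neither |

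The last row uses the primes and test pair that the Procedure itself gives, and it is neutral. The first three cross examples from different sections. If the aardvark is the target, the first two rows reverse direction.

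**Step 4: scale, by assumption only.** The documents give no effect for a single related prime, so suppose a net No Priming shift of 2, 4 or 6 points over an infant's trials. The plan has 24 infants per condition. The pilot states SD 8 points, but its mean of 64%, t = 5.5 and n = 18 imply 14 × √18 / 5.5 = 10.8, so both are shown. With SE = SD × √(2/24) for two groups and SD / √24 for one, two-sided alpha .05 and noncentral t (a simplification of the planned mixed model), the chance of a significant result from the shift alone is:

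| Net shift | Two groups, SD 8 | Two groups, SD 10.8 | No Priming vs 50%, SD 8 | No Priming vs 50%, SD 10.8 |
|---|---|---|---|---|
| 2 points | 14% | 10% | 22% | 14% |
| 4 points | 40% | 24% | 65% | 41% |
| 6 points | 72% | 47% | 94% | 74% |

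The table shows why a modest shift would matter. It is not an estimate of one.

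**The case against.** The strongest reply is that nothing shown proves that any infant sees an unbalanced trial. The examples are illustrations: shoe is not among the twelve nouns, furniture is not among the four neighborhoods, and sets from different sections may never meet in one trial. The only primes and test pair given together, in the Procedure, are neutral. The full list is in S3 Appendix, the No Priming figure is not reproduced, and Data preparation mentions counterbalancing schemes whose content is not visible. If omissions were unsystematic, target-side and distractor-side priming would be equally frequent for in-set pairs, and half of the choices would name both objects. With outside distractors, a tilt can only go toward the target, which works against the authors' hypothesis. The disputed sentence can also be read as saying only that no one neighborhood is favored over the others.

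Most of this stands, and it limits the point. A reader might infer that the No Priming baseline is in fact tilted, or tilted in favor of the hypothesis. The documents support neither inference.

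It does not rescue the argument in the text. Even on the milder reading, three primes favor three neighborhoods over the fourth, and that matters whenever one test object lies in the omitted neighborhood and the other does not. Nor is cancellation assured. Leaving out the target's neighborhood, as the Procedure's own example does, is neutral with an outside distractor; applied to in-set pairs, it would prime the distractor on every trial. The text shown has no rule against that.

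**Conclusion.** The point holds as a defect in the stated selection rule, not as a demonstrated bias. Different neighborhoods among the primes do not imply neutrality between the test objects. For in-set pairs, half of the possible choices are one-sided and none leaves both objects unprimed. For outside distractors, three quarters are one-sided, all toward the target. These fractions count possible choices under the stated rule; they are not frequencies in the actual stimuli.

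The net direction and size of any effect on Semantic Priming minus No Priming, or on the 50% prediction, cannot be determined without S3 and a one-prime effect. The conclusion assumes that the four neighborhoods are as listed and that one related prime can carry some cue. Because the comparator is central and an imbalance in the stimuli could not be removed after collection, the rule should be corrected beforehand.

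**What to change.** Replace the criterion that the primes come from different neighborhoods with a rule tied to the test pair: in every No Priming trial, either both test objects' neighborhoods are among the three primes, or neither is.

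- **Both test objects within the four:** prime both. For example, use fruit–animal and clothing–vehicle pairs twice each, with roles swapped, and the prime sets {fruit, animal, clothing}, {fruit, animal, vehicle}, {clothing, vehicle, fruit} and {clothing, vehicle, animal}. Each neighborhood appears in three sets, so 4 × 3 = 12 and each noun is used once.
- **Distractor outside the four:** leave out the target's neighborhood, so that neither object is primed.

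Reword the neutrality sentence to say that the primes do not favor either test object, since balanced pairs do name both neighborhoods. Check S3 against the rule before data collection, which the Timeline places after in-principle acceptance, and reassign nouns only where a trial fails. If S3 already complies, stating the rule is enough.

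The cost is the check and possibly re-cutting some No Priming videos. No extra infants or trials are needed. Experiment 2 inherits the correction.

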**Fig 2 pone.0244968.g002:**
[figure not shown]
A representative example of visual and linguistic information presented in each phase in the no priming condition.

Follow-up Control condition (*N* = 24): Although our pilot data (see below) suggest that 15-month-olds successfully establish novel object representations based on language input alone, it is important to rule out the possibility that their success is driven by the semantic relations among the objects themselves and therefore not dependent upon infants’ inferences about novel word meanings. We therefore plan a Follow-up Control condition, identical to the Semantic Priming condition with one exception: during Test, infants will hear a novel word that differs from that presented on Trial 4. If infants’ object preference at test is driven by the objects themselves, rather than naming, then performance in this Follow-up Control should not differ from that in the Semantic Priming condition. Conversely, if performance in the Semantic Priming condition is a consequence of verbal reference, then performance in this Follow-up Control condition should not differ from that in the No Priming condition.

#### Data preparation

We will analyze infants’ looking behavior from the onset of the image presentation through the end of the trial (6 s). Our decision to conduct 6 s of image presentation in test trials is based on prior evidence: Ferguson et al. (2014) [27] tested infants of comparable age in a procedure that also involved establishing word meanings in the absence of a visible referent. As in Ferguson et al., trials on which the total looking to the screen is less than 1s will be excluded from analyses.

For data collected in the lab using a Tobii T60XL eyetracker, we identify areas of interest (AOI) of approximately 720*790 pixels around each of the object images, such that every AOI includes a 50-pixel-wide area around an object image. This is done to accommodate for imprecisions of the eyetracking data, which often result from infants’ head movement or blinking. Gazes outside these areas will be excluded from analysis, as will be trials in which an infant’s total looking time is less than 1 out of 6 seconds.

For data collected on Lookit, manual frame-by-frame coding will be performed by trained research assistants who will watch video-recordings of online testing sessions and determine whether the infant is looking to the left or to the right side of the screen during each frame. Depending on the location of the target object, left-right codes will then be converted to target-distractor codes by a different research assistant. Ten percent of all videos will be selected for reliability coding. All research assistants involved in video coding will be agnostic to experimental conditions or counterbalancing schemes.

For each trial of each infant, we will calculate the proportion of looking time devoted to the target [looking to target/(looking to target + distractor)] throughout the analysis window. This should yield up to 4 data points for each infant (one per each of 4 trials). To assess the time course of infants’ attention to the animal and artefact images, eyetracker data will be aggregated by condition into a series of 100-ms bins. For data collected on Lookit, we will use 200-ms bins. Web-cameras typically have sampling rates varying between 30HZ and 60HZ, which translates to frame duration ranging from 16.67 ms to 33.33 ms. Binning our data into 200-ms segments allows us to have at least 6 frames in each bin and to calculate the proportion of infants’ looking to the target image. Fewer frames per bin would result in substantially cruder estimations of infants’ proportion of looking to the target.

#### Analyses

The *dependent variables* (DVs) will be [1] infants’ proportion of looking time (LT) to the target image from the image display onset until 6 s later, averaged across four trials; [2] the time course of the proportion of LT for each 100-ms (or 200-ms) bin in the 6-s window. Because our goal is to evaluate the effect of semantic priming on infants’ word learning under the conditions of displaced reference, we will use Condition as the main *independent variable* (IV).

In analyzing the overall proportion of LT to the target, we will use a Generalized Linear Mixed Model (GLMM) with Condition as a fixed factor and Participant and Test Item as a random factors. We include the Test Item variable to account for the potential effects of infants’ knowledge in different domains–fruits, vehicles, clothing, and animals. We plan to use an identity link, which will require that we test the distribution of the data for normality. We will implement this by running a Shapiro-Wilk test. If the distribution of our data significantly deviates from normal, an appropriate transformation will be applied. In analyzing the time course, we will use the cluster-based permutation analysis [40] to identify significant divergences between the conditions that correspond to mention of the target word.

The effects of demographic factors, vocabulary scores, and trial order will be tested in a preliminary analysis, implemented by fitting a GLMM to the DVs. Trial order is included to test whether infants’ looking preferences change over the duration of the procedure, as they might lose interest or exhibit a learning effect as the experiment progresses. Only the factors that produce significant effects in the preliminary analysis will be included in the main analyses. No other analyses are planned for the data collected via the demographic survey.

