#### Participants

Seventy-two (*N* = 24 per condition) infants from the Chicago area will be recruited from the laboratory database. Infants will have no more than 15% exposure languages other than English. Caregivers will complete a MacArthur Short Form Vocabulary Checklist: Level II [Form A; 32], augmented with words used in the experiments but not included in the form (see S1 Appendix). They will also complete a demographic questionnaire about their education, employment, gender, and race (see S2 Appendix).

The number of participants was determined based on power analysis performed with G*Power 3.1 [33] for a repeated measures between-subject F-test with target effect size *f*^2^ = .1225 (medium; [34], *alpha* = .05, power = .8, number of groups (experimental conditions) = 3, number of trials = 4, and projected correlation between measurements = .5. We reasoned that compelling evidence would require at least a medium effect size of experimental condition. Based on these parameters, the required number of participants is 72. The planned analyses include Generalized Linear Mixed Model rather than an F-test. We used F-test-based effect size estimations for simplicity. The four test trials were treated as repeated measures.

Participants may be excluded and replaced due to fussiness, crying, or equipment failure. Further, because our Covid-19 Contingency Plan (see below) involves testing infants using Lookit–an online platform designed for developmental research–we expect a data loss rate of about 47–50% [35] due to infants’ crying or fussiness, parental interference, or technological issues. This, we anticipate that the total number of infants recruited could reach 140.

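### Target side varies between trials but is in neither the GLMM nor the screened factors, so infants' side bias can cost the Condition comparison some precision

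*Protocol article*

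**What the plan says.** The Analyses section for Experiment 1 specifies a GLMM for the proportion of looking to the target, "with Condition as a fixed factor and Participant and Test Item as a random factors". It adds: "The effects of demographic factors, vocabulary scores, and trial order will be tested in a preliminary analysis". Of these factors, only the significant ones enter the main model. Target side is in neither list.

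The Procedure section shows the two test objects next to each other. Under Data preparation, the Lookit coding is described as follows: "Depending on the location of the target object, left-right codes will then be converted to target-distractor codes". So target location is not constant, and it is known for every trial. The same section says that coders will be "agnostic to experimental conditions or counterbalancing schemes". That is the only mention of counterbalancing, and the article does not say what is balanced.

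The Participants section of Experiment 2 carries the same analyses forward.

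**The concern.** An infant who favours one side has a raised target proportion when the target is on that side and a lowered one when it is not. The plan treats test item and trial order as possible nuisance influences but leaves out this one.

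Side bias can widen the standard error (SE) of the Condition contrast in two ways:

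- If an infant's analysed trials are not split evenly between sides, the bias does not cancel and adds real noise to that infant's mean.
- If they are split evenly, the bias cancels from the mean but inflates the within-infant residual. When that residual becomes large relative to the spread between infants, the Participant variance is estimated as zero and the reported SE is too large.

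The Predictions section draws conclusions from non-differences: Follow-up Control against Semantic Priming, and the control conditions against chance. A needlessly wide SE makes such results easier to obtain.

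**Working it through.** **1. The plan's own figure.** The Participants section gives "target effect size *f*^2^ = .1225", three groups, four trials and "projected correlation between measurements = .5", and concludes: "Based on these parameters, the required number of participants is 72". For a between-subject F-test with repeated measures, λ = f²·N·m / (1 + (m − 1)ρ). At N = 72 this is .1225 × 72 × 4 / 2.5 = 14.11 on 2 and 69 df, which gives power of 91.9%. Power of 80% is reached at N = 53, or 54 in equal groups. So 72 does not reproduce. That is a separate matter and errs towards more power. Only ρ = .5 is carried forward here.

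**2. Inputs for the side check.**

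- From the protocol: 24 infants per condition, four trials, ρ = .5, Condition between subjects.
- Assumed, because the documents give no figure: an average side effect of 3 points and a between-infant side-bias SD of 6–10 points (15 as an extreme). Each is the shift up or down from the infant's own mean.
- Assumed infant-mean variance before side bias: 16 + 324/4 = 97, an SD of 9.8 points. The Pilot data section states an SD of 8; its t of 5.5 for 64% against 50% with 18 infants implies 14 × √18 / 5.5 = 10.8.

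Two variance splits give the same 97:

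- ρ = .5: total variance 97/.625 = 155.2, so Participant 77.6 and residual 77.6.
- ρ near .05: Participant 16, residual 324, and 16/340 = .05.

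The SE of a Condition contrast without side bias is √(2 × 97/24) = 2.84.

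**3. Sides 2/2, all trials present, SD 10** (Test Item left out of the algebra). The between-infant mean square is 4 × 97 = 388, which side bias does not alter. The within-infant mean square rises by (4/3)(10² + 3²) = 145.3.

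- ρ = .5: within = 77.6 + 145.3 = 222.9, below 388. The Participant variance is estimable and the SE stays at √(388/48) = 2.84. Simulation with 4,000 replicates gave 2.82 with and without side.
- ρ near .05: within = 324 + 145.3 = 469.3, above 388. The Participant variance is set to zero and the mean squares are pooled: (69 × 388 + 216 × 469.3)/285 = 449.6. The SE becomes √(449.6/48) = 3.06, against 2.84, or 8% too wide. REML simulation gave 3.07 against 2.84.

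At ρ = .5 the threshold is reached only near SD 15: 77.6 + (4/3)(15² + 3²) = 389.6. Simulation there gave 2.91 against 2.82, about 3%.

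**4. Sides 2/2, trials lost, ρ = .5.** With 20% lost and SD 10, REML gave 3.09 as planned against 3.02 with side and slope, 2% too wide. A known-variance calculation with 25% lost gave 1.1%. It used a left–right difference with an SD of one single-trial SD, which is √155.2/2 = 6.2 points each way.

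**5. Side randomised per trial, ρ = .5, SD 10.** The infant-mean variance rises by (10² + 3²)/4 = 27.25 to 124.25, so the SE is √(2 × 124.25/24) = 3.22. Simulation gave 3.17 as planned against 2.93 with side and slope (8%); a second run gave 3.23 against 3.00. At 6.2 points the known-variance figure was 3.1%, of which a fixed side term alone recovered 1.1%.

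| Layout | ρ | Side-bias SD | SE too wide by |
|---|---|---|---|
| 2/2, complete | .5 | 10 | 0% |
| 2/2, 20–25% lost | .5 | 6–10 | about 1–2% |
| Random per trial | .5 | 10 | about 8% |
| 2/2, complete | near .05 | 10 | about 8% |

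**6. Cost of the term when it is not needed.** With no between-infant side-bias spread (2/2, complete, ρ near .05), the SE was 2.85 as planned and 2.84 with side.

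**The case against.** The strongest case against is that Condition is randomised between infants. If targets are balanced 2/2, side bias drops out of each infant's mean, and at the protocol's own correlation of .5 nothing is lost. The 8% under balanced sides needs a correlation near .05, which conflicts with that figure. This stands, and it is why the point is minor.

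Three further objections have some weight:

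- **Layout and covariates are often left to a fuller document.** This stands for the layout. It does not for the model: the Analyses section states the model terms and the factors that may be added.
- **The outcome is described as averaged across four trials, so there is no within-infant residual.** The random Participant and Test Item terms, and the up to four data points per infant under Data preparation, point to a trial-level model.
- **A by-Participant slope from at most four trials is fragile, and a fixed term alone removes only the average bias.** Both parts are true, and the fix allows for them.

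A reader might infer that the planned analysis is certain to lose precision, or that the Condition effect is biased. The documents support neither. They do not say how sides are laid out or how strong side bias is, and random assignment keeps side from favouring any condition. Nor does the text establish that the counterbalancing covers side; that is a reasonable inference from one phrase about coders.

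**Conclusion.** The omission is real: target side varies, is known for every trial, and has no route into the model. The consequence is a possible loss of precision in the Condition comparison, not an error in its estimate.

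Under the assumptions above, the loss runs from nothing to about 8% of the SE at a side-bias SD of up to 10 points. Some trial loss is foreseeable, because trials with under 1 s of looking are dropped. With balanced sides and the stated correlation, that puts the likely cost at 1–2%. The larger figures need sides randomised per trial or a trial correlation far below .5. All of this rests on assumed side-bias values. It is a minor improvement, worth making because it is nearly free.

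**What to change.** In the Analyses section, and so for Experiment 2, add Target Side (left/right) to the trial-level GLMM as a prespecified fixed factor, kept whatever its significance. Add a by-Participant side slope where it can be estimated. Otherwise keep the fixed term alone, and note that it removes only the average bias.

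The cost is a line of text and one or two extra parameters, with a possible convergence problem because each infant gives at most four trials. Target side is already recorded for scoring, so no new data are needed.
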